#### Time to remissionand time to response analysis

To assess differences in time to remission, we will utilize survival analysis techniques. Participants will be categorized based on the number of weeks until remission (1 week, 2 weeks, 3 weeks, or censored if not reached within the treatment duration). Kaplan–Meier survival analysis will be employed to visualize the probability of achieving remission over time between treatment conditions (*Light@Home*,* LightCafé*, and *LightCafé* +). Additionally, we will apply Cox proportional hazards modelling to evaluate the effects of treatment condition and covariates (age, gender, clinical diagnosis) on the time to remission (outcome). Results will be presented with survival curves and hazard ratios. Similar analyses will be conducted on time to response.

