### Eligibility criteria {10}

#### General eligibility criteria

Eligibility will be assessed during the intake by study team members trained in administering the MINI International Neuropsychiatric Interview 5.0.0 (M.I.N.I.; [69]). The inclusion criteria are as follows:Age between 18 and 65.Diagnosis of unipolar or bipolar depression (seasonal or non-seasonal) confirmed by the M.I.N.I. [69].Currently experiencing a depressive episode, as indicated by a Quick Inventory of Depressive Symptomatology Self-Report (QIDS-SR; [70]) score of 6 or higher.Proficiency in either Dutch or English is required for questionnaire completion.

Participants are excluded from participation if they:Are currently experiencing a (hypo)manic or mixed episode, as determined by the M.I.N.I. assessment [69].Are presently in a psychotic episode, as determined by the M.I.N.I. assessment [69].Exhibit significant active suicidality, indicated by a score of 10 or higher on the M.I.N.I. module [69].Initiated antidepressant therapy (including medication, psychotherapy, BLT, or other specific depression treatments) within the last 2 months prior to study enrolment.Have a bipolar disorder but are currently not under mood-stabilizing treatment for at least 1 month at the recommended dosage.Have used melatonin or agomelatine in the past month.Are currently using antibiotics.Are currently taking medications that increase light sensitivity.Have travelled across more than one time zone in the past month or during the treatment period.Have travelled to sunny holiday destinations or engaged in outdoor winter sports in the past month.Have pre-existing eye and skin disorders such as retinitis pigmentosa, porphyria, chronic actinic dermatitis, and sun-induced urticaria.Have systemic disorders with potential retinal involvement, such as rheumatoid arthritis and systemic lupus erythematosus.Have color blindness (based on self-report).Worked night shifts within the last three months.Suffer from (retinal) blindness, severe cataracts, or glaucoma.Experience light-induced migraine or epilepsy.Are currently pregnant or have a child Younger than 18 months old.

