### Intervention description {11a}

In all study arms, participants are subjected to BLT in adherence to Dutch BLT guidelines [72], utilizing an Innolux LED light Lamp delivering light with an illuminance of 10,000 lx at a distance of 70 cm and a color temperature of 3800 K. BLT sessions, lasting 30 min each, are scheduled from Monday to Friday between 7:30 AM and 10:30 AM.

The number of BLT sessions is contingent upon the individual response of each participant, with a maximum duration of 3 weeks. Initially, participants undergo five consecutive BLT sessions during the workweek. Subsequently, the therapeutic efficacy is evaluated utilizing the QIDS-SR during the Friday session. If the QIDS-SR falls below 6, remission is inferred, leading to the termination of BLT. Alternatively, an additional five sessions are administered. This evaluation and decision process is repeated at the end of the second week. If the QIDS-SR score is still above 6, a third and final week of treatment is provided.

This individualized strategy is intended to reduce the small risk of (hypo)manic switches, which occur in less than 2% of bipolar patients and almost exclusively in those not maintained on mood stabilizers [11, 73]. We will continuously monitor for (hypo)manic symptoms using the Young Mania Rating Scale (YMRS; [74]) and clinical observation: a YMRS score ≥ 13 and clinician‐identified symptoms will lead to immediate treatment cessation, while scores of 10–11 will prompt a joint review with a second clinician to decide on discontinuation [75, 76].

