### Outcomes {12}

#### Primary study outcome—clinical improvement in depressive symptoms

The primary outcome of this study is the clinical improvement in depressive symptoms assessed with the Montgomery Åsberg Depression Rating Scale (MADRS; [78]) from baseline to post-treatment. Independent raters, unaware of participants’ treatment conditions and assessment points, will conduct MADRS evaluations. Other key metrics based on the MADRS include remission (participants with post-treatment scores of 10 or lower [79]) and response rates (participants with 50% reduction in depressive symptoms from baseline to post-treatment assessment).

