### Treatment phase

During the treatment phase, participants receive 1, 2, or 3 weeks of BLT within their assigned condition. Every Friday, depressive symptoms are assessed using the QIDS-SR, regardless of whether the participant received treatment that week. Treatment will be continued as long as QIDS-SR-score is higher than 6, with a maximum of 3 weeks. Treatment tolerability and mania symptoms are assessed using the YMRS after each week of BLT. EMA, actigraphy, and light logger usage continue throughout the treatment.

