### Secondary Study Outcomes

#### Subjective Assessment of Depressive Symptoms, Relapse Rates and Functional Outcomes

Multilevel mixed-effects models will be constructed to assess depressive symptom improvement, measured weekly during therapy and at follow-up assessments using the QIDS-SR scores as the dependent variable. Fixed effects will include timepoint as an categorical variable (baseline, 1 week, 2 weeks, 3 weeks, 4 weeks, 10 weeks, and 4 months), and the interaction between timepoint and treatment condition (*Light@Home*,* LightCafé*, and *LightCafé* +). Random intercepts and slopes will be included for participants and study centers, as well as random slopes for time within participants, based on model fit criteria. Confounding variables (age, sex, clinical diagnosis, and credibility/expectancy of treatment) will also be evaluated and included as necessary. A variable will be added to account for treatment duration (1 week, 2 weeks, 3 weeks). Similar models will be considered for analyses of relapse rates, functional outcome, and Quality of Life with inclusion of the respective timepoints as fixed effects (see Table 1).

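### Censoring time to response at the end of the patient's own treatment would remove some mild patients from the risk set because they improved; the window should be fixed at weeks 1 to 3

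*Protocol article*

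**What the plan says.** The section on time to remission and time to response places each participant in one of these categories: "1 week, 2 weeks, 3 weeks, or censored if not reached within the treatment duration". It gives response no event definition and no censoring rule of its own: "Similar analyses will be conducted on time to response".

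Treatment length depends on the outcome. Under Intervention description {11a}, "If the QIDS-SR falls below 6, remission is inferred, leading to the termination of BLT", with 3 weeks as the maximum. The Treatment phase section words the rule differently: "Treatment will be continued as long as QIDS-SR-score is higher than 6, with a maximum of 3 weeks".

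The QIDS-SR schedule does not depend on treatment: "Every Friday, depressive symptoms are assessed using the QIDS-SR, regardless of whether the participant received treatment that week". Entry requires a QIDS-SR "score of 6 or higher". Response is defined only for the MADRS, as "participants with 50% reduction in depressive symptoms from baseline to post-treatment assessment".

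**The concern.** The censoring rule was written for remission and suits it: remission ends treatment and is also the event. Carried over to response, the same rule lets treatment end on a different event. A patient can meet the remission threshold, stop light therapy, and not yet have halved the entry score. If follow-up for response then stops, that patient leaves the risk set because of doing well.

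Kaplan-Meier and Cox models need censored patients to have the same later chance of response as patients who stay at risk. Here the censored patients have just improved and sit close to the response threshold, while most of those still at risk have not remitted. Responses seen on later Fridays would be collected but not counted, and the response curves would be too low.

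**Working it through.** **1. Which duration is meant.** The time-to-event section does not say. Two other places use the term for the individual patient: the Methods part of the Abstract, where it ranges from one to three weeks according to response, and the QIDS-SR model, where "A variable will be added to account for treatment duration (1 week, 2 weeks, 3 weeks"). Intervention description {11a} also gives a 3-week maximum. The individual reading is the more natural one, and the steps below follow it.

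**2. Which scale is meant.** Table 1 shows the MADRS only at B1 and PT1, so it cannot supply weekly event times. The section on mood-related and functional outcomes takes self-rated response from the QIDS-SR. The 50% criterion is therefore borrowed from the MADRS definition.

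**3. Where remission and response part.** Response needs a score ≤ entry/2. Stopping needs a score ≤ 5 (below 6).

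| Entry QIDS-SR | Response needs | Stops without response |
|---|---|---|
| 6 | ≤ 3 | 4, 5 |
| 7 | ≤ 3 | 4, 5 |
| 8 | ≤ 4 | 5 |
| 9 | ≤ 4 | 5 |
| 10 or more | ≤ 5 or higher | none |

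Example: entry 8, week-1 score 5, week-2 score 3. Light therapy stops at week 1 and the patient is censored. The week-2 score is a response (3 ≤ 4) but is not counted.

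Under the Treatment phase wording, a score of exactly 6 also stops treatment. Entry at 10 or 11 (response needs ≤ 5) is then affected too, and the band widens from 6–9 to 6–11.

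**4. Size.** The plan gives no figure for this analysis, so there is none to reproduce. The following was simulated with 200,000 patients per setting. All inputs are assumptions, not taken from the documents: entry score normal with mean 10, 13 or 16 and SD 4, limited to 6–27; mean weekly fall 1.5, 2.0 or 2.5 with between-patient SD 1.2; weekly noise SD 2; stop below 6.

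| Entry mean | Censored at week 1 or 2 without response | Week-3 response, all followed (fall 1.5 / 2.5) | Kaplan-Meier, censored at own treatment end (fall 1.5 / 2.5) | Understatement (points) |
|---|---|---|---|---|
| 10 | about 11% | 49.6% / 74.1% | 45.9% / 71.3% | 3.7 / 2.8 |
| 13 | about 5% | 38.0% / 63.5% | 36.2% / 62.0% | 1.8 / 1.5 |
| 16 | about 1% | 26.2% / 50.5% | 25.6% / 50.0% | 0.6 / 0.5 |

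Of those entering at 6–9 who remitted at week 1 or 2, 33% to 44% were censored without response. The rest had a response event.

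**5. Is the censoring informative?** In the same model, patients censored at week 1 had roughly a 51% to 71% chance of responding at week 2, against 9% to 38% for those still at risk. Of all patients censored at week 1 or 2, 68% to 86% responded by week 3.

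**6. Effect on the arm comparison.** Two arms were simulated with different weekly falls. The hazard ratio for the faster arm, with full follow-up and then with censoring, was:

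| Entry mean | Falls 1.5 and 2.5 | Falls 2.0 and 2.25 |
|---|---|---|
| 10 | 1.96 → 2.01 | 1.19 → 1.20 |
| 13 | 2.08 → 2.13 | 1.22 → 1.23 |
| 16 | 2.28 → 2.30 | 1.23 → 1.23 |

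The largest shift is 2.01/1.96 = 1.026, under 3%, and it favours the faster arm.

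**The case against.** The strongest reply is that the document never states this rule for response. It says only that similar analyses will be done, and an analysis plan could supply the event definition and the censoring time. For remission, patients who have not remitted are treated to week 3, so the individual and maximum durations coincide apart from stops by staff or for mania symptoms. The categories of 1, 2 and 3 weeks match the Friday schedule, and the plan is intention-to-treat. On the 3-week reading the problem vanishes. This stands as a genuine alternative. It does not remove the point, because a censoring rule is in print, it is carried to a second endpoint, and the document's other uses of the term point to the individual duration.

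Three stronger readings are tempting, and the documents do not support them.

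- A reader might infer bias against the better arm. The simulated hazard ratio moves by less than 3%, and slightly the other way. Faster improvers more often reach remission and response together, so the early-censored shares are nearly equal between arms (11.1% and 10.7% at entry mean 10).
- A reader might count everyone entering at 6–9 as affected, or call them counted as non-responders. Only those who stop above half their entry score are affected, and they leave the risk set without being scored as failures.
- A reader might extend the harm to time to remission. There the stop is itself the event. Only patients stopped for other reasons could lose a later remission, and the protocol puts (hypo)manic switches below 2% of bipolar patients.

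**Conclusion.** The point holds as a minor one on a secondary, self-rated endpoint. If the patient's own treatment duration ends follow-up for response, censoring is triggered by improvement and is informative, and responses already observed are discarded. Under the assumed entry scores, about 1% to 11% of patients are affected (about 3 to 26 of 231: 0.013 × 231 = 3.0; 0.112 × 231 = 25.9). Week-3 Kaplan-Meier response is then understated by about 0.5 to 4 percentage points, most in a mild sample. The supported harm is to the response curves and to the censoring assumption; no meaningful distortion of the comparison between arms is shown.

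This rests on three things: the individual reading of treatment duration, the 50% MADRS criterion applied to the QIDS-SR, and the assumed entry scores and rates of fall. The 6–9 band itself is exact arithmetic under the below-6 stopping rule. The primary MADRS analysis and the MADRS-based response and remission analyses are untouched.

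**What to change.** In the section on time to remission and time to response, replace the reference to treatment duration with a fixed window. Both endpoints would run over weeks 1 to 3 from the start of treatment for every randomised participant, using the Friday QIDS-SR whether or not light therapy is still being given, with censoring only at week 3 or at the last completed QIDS-SR. State that response here is a 50% reduction in QIDS-SR from a named baseline, since the scale is taken at both Intake and B1.

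Separately, Intervention description {11a} and the Treatment phase section differ at a QIDS-SR of exactly 6 and must be reconciled, because the answer sets which patients can stop without a response.

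The change to the analysis costs a sentence or two and no new data, as the off-treatment Friday scores are already scheduled. The article reports the trial as still enrolling, so the rule can be set before outcomes are analysed.

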## Mood-related and functional outcomes

Complementary to the clinician-rated depressive symptoms, self-reported depressive symptoms will be evaluated using the QIDS-SR, administered weekly from baseline to post-treatment, as well as at the 10-week and 4-month follow-ups. In addition to tracking self-reported depression scores over time, we will utilize QIDS-SR data to assess self-rated remission rates, self-rated response rates, time to remission, and relapse rates.

Momentary affect measures are evaluated using EMA to assess mood throughout the day. From the baseline week through 1 week after treatment, participants receive eight daily smartphone alerts containing items from the Positive and Negative Affect Scale [80] the Activation-Deactivation Adjective Check List [81] and additional items adapted specifically for this EMA. Momentary Positive Affect (PA) is assessed using the average score of three items in the EMA: “I feel cheerful,” “I feel content,” and “I generally feel well,” each rated on a 7-point scale from 1 (*not at all*) to 7 (*very*). Momentary Negative Affect (NA) is evaluated using the average of six items: “I feel irritated,” “I feel insecure,” “I feel lonely,” “I feel anxious,” “I feel down,” and “I feel guilty,” rated similarly. Diurnal mood variations will be assessed by comparing momentary affect states in the morning with momentary affect in the afternoon and evening.

Functional outcomes will be evaluated using the Short Form Health Survey (SF-12; [82]), the Mental Health Quality of Life Questionnaire (MHQoL; [83]), at baseline, post-treatment, and during follow-up, providing us with parameters for overall functioning and quality of life, respectively.

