## Assignment of interventions: allocation

### Sequence generation {16a}

Eligible participants are randomized using block randomization via the Research Manager data platform [94]. To ensure a balanced distribution among treatment groups and minimize potential biases, participants are stratified based on several key factors, including chronotype (categorized as early, intermediate, or late based on the MEQ [86], clinical diagnosis (differentiating between unipolar and bipolar conditions according to the M.I.N.I. assessment), and participation in the melatonin assessment (indicated as either yes or no).

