The following questionnaires and rating scales will be used during the study:**Mini-International Neuropsychiatric Interview (M.I.N.I.) PLUS 5.0** [69]: The M.I.N.I. is a brief, structured diagnostic interview designed to generate DSM-5 psychiatric diagnoses in approximately 30 min. It covers mood disorders (bipolar I & II, major depression, suicidality), anxiety disorders (social anxiety, panic, agoraphobia, generalized anxiety, PTSD, OCD), ADHD, eating disorders (anorexia, bulimia), substance use disorders (alcohol and other substances), and psychotic disorders. Its modular format allows rapid, reliable case‐finding in clinical trials and epidemiological studies. Test–retest reliability coefficients for major depression and anxiety diagnoses typically exceed *κ* = 0.70, and it shows good concordance with longer interviews such as The Structured Clinical Interview for DSM-5 [95]**Montgomery–Åsberg Depression Rating Scale (MADRS)** [78]: The MADRS is a clinician‐administered 10-item scale that quantifies depressive symptom severity over the preceding week. Each item (e.g., apparent sadness, inner tension, sleep, and appetite disturbances) is rated 0–6, yielding a total score from 0 to 60. The MADRS exhibits excellent inter‐rater reliability (ICC > 0.90) and sensitivity to treatment-induced change, making it a standard in antidepressant trials.**Quick Inventory of Depressive Symptomatology–Self-Report (QIDS-SR)** [70]: The QIDS-SR comprises 16 items mapping the nine core DSM-5 depressive domains (sad mood, anhedonia, concentration, self‐view, suicidal ideation, energy, sleep, appetite/weight, psychomotor changes) over the past 7 days. Responses use a 0–3 Likert scale, with composite scoring algorithms yielding a 0–27 total. Internal consistency is high (Cronbach’s *α* = 0.86–0.89), and the QIDS-SR correlates strongly with both the MADRS and HAM-D (*r* > 0.80), supporting its validity as a brief self‐report measure of depression severity.**Morningness–Eveningness Questionnaire (MEQ)** [86]: This 19-item self-report evaluates an individual’s circadian preference—“chronotype”—by asking about preferred timing for sleep, wakefulness, and peak performance. Scores classify respondents from “definite evening type” to “definite morning type.” The MEQ demonstrates good internal consistency (*α* ≈ 0.80) and has been validated against objective markers such as dim‐light melatonin onset.**Ultra-Short Munich Chronotype Questionnaire (μMCTQ)** [87]: The μMCTQ estimates chronotype via six items: usual sleep onset andsimi of work versus free days. By calculating the midpoint of sleep on free days corrected for accumulated sleep debt, it yields an estimate of intrinsic circadian phase. Test–retest reliability for sleep timing variables exceeds *r* = 0.90, and μMCTQ midpoints correlate well with full MCTQ scores.**Pittsburgh Sleep Quality Index (PSQI)** [84]: The PSQI is a 19-item self-report assessing sleep quality and disturbances over the past month across seven domains: subjective sleep quality, latency, duration, habitual efficiency, disturbances, medication use, and daytime dysfunction. Global scores > 5 indicate poor sleep. The PSQI’s internal consistency is acceptable (*α* = 0.75–0.83), and it discriminates insomniacs from healthy controls with a sensitivity of 89.6% and specificity of 86.5%.**Insomnia Severity Index (ISI)** [85]: The ISI consists of seven items rated 0–4 that probe the severity, impact, and perceived distress of insomnia symptoms. Total scores range from 0 to 28, with higher scores reflecting more severe insomnia. Internal consistency is excellent (*α* = 0.90), and the ISI correlates strongly with sleep diary metrics and polysomnographic indices, validating its use as a brief screening and outcome measure.**Consensus Sleep Diary(CSD)** [77]: A standardized daily log, the Consensus Sleep Diary captures subjective sleep–wake parameters—sleep onset latency, wake after sleep onset, total sleep time, time in bed, number and duration of awakenings, and morning sleep quality/refreshed ratings. It is the recommended unifying sleep diary for research, showing excellent agreement (*r* > 0.80) with actigraphy and flexibility for both EMA and weekly retrospective summary at follow‐up visits [77].**Short Form Health Survey (SF-12)** [82]: Derived from the SF-36, the SF-12 yields two summary scores—Physical Component Summary (PCS) and Mental Component Summary (MCS)—from 12 items covering domains such as physical functioning, role limitations, bodily pain, vitality, social functioning, and mental health. Despite its brevity, the SF-12 explains over 90% of the variance in SF-36 summary scores, exhibiting high test–retest reliability (ICC > 0.70) and construct validity across diverse populations.**Mental Health Quality of Life (MHQoL)** [83]: The MHQoL is a seven-dimension, four-level descriptive system (MHQoL-7D) plus a visual analogue scale (MHQoL-VAS, 0–10) for overall psychological well-being. Dimensions include self-image, independence, mood, relationships, daily activities, physical health, and outlook. It demonstrates good feasibility, content validity for mental health populations, and sensitivity to clinical change.**Credibility/Expectancy Questionnaire (CEQ)** [71]: The CEQ measures perceived treatment credibility and expectancy via six items: three assess credibility on a 1–9 scale and three assess expectancy on a 0–100% scale. Internal consistency ranges from *α* = 0.79 to 0.90, and early expectancy ratings predict clinical outcomes across psychotherapy and pharmacotherapy trials, underscoring its utility as a prognostic indicator.**Young Mania Rating Scale (YMRS)**: The YMRS is an 11-item clinician interview that quantifies manic symptoms—elevated mood, sleep, irritability, speech, thought content, motor activity, and insight. Items are weighted according to severity and duration (total score 0–60). Inter‐rater reliability is excellent (ICC > 0.85), and sensitivity to mood changes renders the YMRS a benchmark for bipolar disorder trials [74].**Adverse Event Scale for Light Therapy***:* A custom checklist will record the presence, frequency, and severity of known side effects of bright light exposure (e.g., headache, eyestrain, nausea), using Likert‐type ratings to facilitate systematic monitoring of tolerability throughout the intervention period.

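### The Cox model for time to QIDS-SR remission leaves out the baseline QIDS-SR, which costs efficiency in a secondary analysis but does not make the test invalid

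*Protocol article*

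**What the plan says.** - **Model.** The section on time to remission and time to response plans Kaplan–Meier curves and a Cox model to "evaluate the effects of treatment condition and covariates (age, gender, clinical diagnosis) on the time to remission". The list carries no qualifier such as 'for example' or 'as necessary'. Similar analyses are announced for time to response.
- **Event times.** Participants are classed as "1 week, 2 weeks, 3 weeks, or censored if not reached within the treatment duration".
- **Source of the endpoint.** Under Mood-related and functional outcomes, QIDS-SR data are to supply "self-rated remission rates, self-rated response rates, time to remission, and relapse rates".
- **Cut-off.** Intervention description {11a}: "If the QIDS-SR falls below 6, remission is inferred, leading to the termination of BLT".
- **Entry.** The eligibility criteria ask for a QIDS-SR "score of 6 or higher" and set no upper limit. The Questionnaires section describes "composite scoring algorithms yielding a 0–27 total".
- **Availability.** The QIDS-SR is "administered weekly from baseline to post-treatment", and Table 1 marks it at Intake and B1.
- **Stratification.** Sequence generation {16a} names chronotype, clinical diagnosis and "participation in the melatonin assessment (indicated as either yes or no"). Severity is not among them.
- **Elsewhere.** Baseline severity is a moderator in the circadian section and a candidate predictor in the section on predictors of response and remission. Baseline is also one of the timepoints in the QIDS-SR mixed model. It is absent only from the Cox model.

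**The concern.** With a fixed cut-off, the fall a participant needs depends on the starting score. Entering at 6 requires a fall of at least 1 point to reach 5; entering at 18 requires 13. There are only three weekly chances to get there. The definition of the endpoint therefore ties the chance of an event to the baseline score, and neither the randomisation nor the model takes account of it.

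Three things follow when a prognostic covariate is left out of a Cox model in a randomised trial: the arm comparison loses power, a chance difference in baseline between arms stays in the estimate, and the estimated hazard ratio lies nearer 1 than the one conditional on that covariate. What is at stake is the precision and interpretation of one secondary comparison.

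**Working it through.** **1. The protocol's own figure.** There is no power, event count or hazard ratio for the Cox analysis to reproduce. The effect size and N come from Sample size {14}: f = 0.25, α = 0.05, power 0.90, N = 210. A one-way noncentral F calculation (three groups, λ = f²N, df 2 and N − 3) gives N = 206, or 207 in equal arms, and power 0.907 at 210. The figure is thus reproduced within 3%, and 210 (70 per arm) is used below.

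**2. Effect sizes.** For three equally spaced arms with extreme difference d (in SDs), f = d/√6, so d = 0.25 × √6 = 0.61 SD. The simr effects in the same section (0.25, 0.33, 0.40) put the extreme arms only 0.40 − 0.25 = 0.15 SD apart.

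**3. Assumptions, none of them in the documents.** Baseline QIDS-SR mean 14, SD 4; SD 5 for scaling effects, so 0.61 SD = 3.06 points and 0.15 SD = 0.75 points; mean fall 6 points; baseline-to-follow-up correlation 0.3, 0.5 or 0.7. Scores are simulated at weeks 1–3; the event is the first score below 6, otherwise censoring at week 3. The Cox model (Efron ties) is fitted with arm only and with arm plus baseline QIDS-SR, using a 2-df likelihood-ratio test for arm. Age, gender and diagnosis are not simulated; any link they have with severity would recover part of the loss.

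**4. Results at N = 210.** Hazard ratios are LightCafé+ versus Light@Home.

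| Effect | Correlation | Power without | Power with | Loss (points) | HR without / with |
|---|---|---|---|---|---|
| f = 0.25 | 0.3 | 66.0% | 70.2% | 4.2 | 1.96 / 2.03 |
| f = 0.25 | 0.5 | 65.0% | 73.8% | 8.8 | 1.92 / 2.10 |
| f = 0.25 | 0.7 | 62.0% | 81.3% | 19.3 | 1.92 / 2.27 |
| simr | 0.3 | 8.0% | 8.7% | 0.7 | 1.18 / 1.18 |
| simr | 0.5 | 8.4% | 9.2% | 0.8 | 1.20 / 1.23 |
| simr | 0.7 | 6.7% | 11.6% | 4.9 | 1.19 / 1.24 |

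The f = 0.25 rows use 600 replicates and the simr rows 900.

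**5. Rough check.** By Schoenfeld's formula, a pairwise comparison of 140 participants with 45% events has 63 events. Power is Φ(√63/2 × ln HR − 1.96): at HR 1.92, Φ(3.969 × 0.652 − 1.96) = Φ(0.63) = 0.74. The simulated pairwise power without baseline is 0.715–0.762.

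**6. Wider grid.** Over 36 scenarios (baseline mean 13–15, SD 3.5–4.5, mean fall 5 or 7, extreme difference 1.5 or 2.5 points, remission 25–61%) the loss is 0.5–6.2 points at correlation 0.3, 1.7–10.8 at 0.5 and 7.8–22.7 at 0.7.

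**7. Under the null (1500 replicates).** The test without baseline rejects in 5.6%, 5.1% and 5.9% at the three correlations. With baseline it rejects in 6.4%, 6.3% and 7.7%, against a Monte Carlo standard error of √(0.05 × 0.95/1500) = 0.6 points. The adjusted fit is thus slightly liberal here, and part of the gain in step 4 reflects that. A rough correction takes the 2-df critical value that matches each observed rejection rate s, −2 ln s (for 7.7%, 5.13 instead of 5.99). It then solves for the noncentrality that gives the observed power and reads the power at 5.99. The power pairs become 64.2/66.4%, 64.7/70.4% and 59.2/75.7%, so losses of about 2, 6 and 17 points.

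**8. Chance imbalance.** With SD 4 and 70 per arm, 95% of differences in baseline mean between two arms lie within ±1.96 × 4 × √(2/70) = ±1.3 points. If SD 5 is also the follow-up SD, the share carried to follow-up is the correlation × 5/4: at 0.5, 1.3 × 0.625 = 0.8 points, about the size of the whole simr effect of 0.75.

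**The case against.** The strongest reply is that nothing is invalid. Arms are randomised, the planned test holds its level, and the trial is sized on the MADRS, not on this analysis. That stands. A reader might infer confounding or a biased test from the omission; the documents and the null results support neither.

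Second, the two hazard ratios answer different questions. Because of non-collapsibility, the one without baseline is less conditional, not a wrong estimate of the other. That also stands, so the value nearer 1 should not be called bias.

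Third, the size is driven by assumptions. This stands too. The upper end needs a correlation near 0.7, and under the simr effects the covariate would hardly change anything. A reader might take the starting score to be the main determinant of remission, or time to remission to be a leading outcome. The first is only an inference from the entry rule and the cut-off, since rate of improvement may matter as much. The second does not fit the Objectives or the abstract, neither of which mentions speed of remission.

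Fourth, the Statistical methods section calls the plan an initial framework open to minor documented changes. That makes the fix easy, but it does not put the covariate into the model. The list as written omits it, although the predictor section treats severity as a candidate predictor of remission.

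**Conclusion.** The point holds as an efficiency matter in one secondary analysis. As written, the Cox model forgoes a baseline covariate that the endpoint's definition makes prognostic and that is already collected. At f = 0.25 and N = 210 the simulated loss is about 4, 9 and 19 points at correlations of 0.3, 0.5 and 0.7 (nearer 2, 6 and 17 after the rough correction for the adjusted fit's null rejection rate). It is about 1 to 5 points under the simr effects. All of this rests on assumed QIDS-SR values. The direction is steadier than the size: the hazard ratio without baseline was nearer 1 in every non-null scenario except one tie.

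A reader might extend the argument to time to response. The documents do not support that equally: response is a relative 50% reduction (defined for the MADRS under Outcomes), so the fixed cut-off reasoning does not apply, and no response endpoint was simulated.

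**What to change.** Add continuous B1 QIDS-SR, linear or as a spline, to the prespecified covariates of the time-to-remission Cox model, and state that the reported hazard ratio is conditional on it. Keep the Kaplan–Meier curves as description. Using it in the time-to-response model is optional.

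Because events fall on only three weekly times and the adjusted fit rejected slightly too often under the null, name the handling of ties and check the test's level by simulation before the model is fixed.

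The cost is one covariate already in the data collection plan and a short documented change. The article describes the trial as still enrolling; the change should be made before outcomes are examined, so that the choice cannot look driven by the data.
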